## Abstract

**Introduction:**

Severe pneumonia caused by multidrug-resistant (MDR) bacteria is associated with high mortality. Inhaled nitric oxide (NO) has antimicrobial activity, but clinical evidence in MDR severe pneumonia remains limited. This trial will evaluate the efficacy and safety of adjunctive high-dose inhaled NO in patients with severe pneumonia associated with MDR bacteria.

**Patients and methods:**

This prospective, single-center, double-blind randomized controlled trial will be conducted at Jiangdu People’s Hospital Affiliated with Yangzhou University from January 2026 to June 2027. Patients with suspected or confirmed severe pneumonia caused by MDR bacteria will be randomized 1:1 to standard treatment plus inhaled NO (200 ppm, twice daily for 30 min/session for 5 days) or standard treatment plus sham inhalation (0 ppm NO). The primary outcome is the change in Clinical Pulmonary Infection Score (CPIS) from baseline to day 7. Secondary outcomes include mortality, 28-day ventilator-free days, vasopressor-free days, antibiotic-free days, ICU-free days, and hospital-free days, CPIS and Sequential Organ Failure Assessment scores, microbiological eradication, citrullinated histone H3 and cell-free DNA concentrations, and ratio of arterial partial pressure of oxygen to fraction of inspired oxygen (PaO_2_/FiO_2_) ratios. Safety outcomes include methemoglobin and NO_2_ thresholds, serum creatinine, airway hyperreactivity, and acute kidney injury. Primary and secondary outcomes will be analyzed in confirmed MDR participants; safety will be assessed in participants receiving at least one study-gas administration.

**Discussion:**

This protocol tests a mechanistically plausible adjunctive therapy for MDR severe pneumonia. It will explore whether high-dose NO affects neutrophil extracellular trap activity.

## Introduction

Multidrug-resistant (MDR) bacterial infection is one of the most important threats to global public health and remains a major unresolved problem in critical care medicine. By 2050, infections caused by MDR bacteria are projected to cause approximately 10 million deaths worldwide each year [1]. Pneumonia is among the most common types of infection. MDR bacterial infection substantially increases the risk of death in patients with pneumonia, particularly among those requiring mechanical ventilation [2].

Nitric oxide (NO) is a colorless, non-irritating gas that is lipid soluble, widely distributed in human tissues, and able to diffuse rapidly across cell membranes. As an intercellular signaling molecule, NO participates in the regulation of multiple physiological processes. When delivered locally at high-dose, inhaled NO also has antimicrobial activity and may provide a potential therapeutic approach for MDR infection [3]. In animal models, short-term high-dose inhaled NO safely and effectively reduced the pulmonary burden of MDR bacteria in mice [4]. Multiple clinical studies have reported that high-dose Nitric Oxide inhalation (160–240 ppm) may exert antimicrobial activity and is associated with reductions in pulmonary bacterial burden [5–7]. A randomized controlled trial reported that inhaled NO at 200 ppm reduced the incidence of hospital-acquired pneumonia after cardiac surgery from 24.3% to 5.4% [8]. Other studies have shown that inhaled NO can improve oxygenation indices in patients with coronavirus disease 2019 [9–11]. A recent clinical study also reported that high-dose inhaled NO did not increase adverse reactions or complications, supporting its potential clinical safety [12] Recently, Yu et al. [13] reported that inhaled NO at 300 ppm exhibited antibacterial activity against MDR bacteria. In this study, no serious adverse events were observed among 10 healthy adults and two critically ill patients [13]. Although high-dose inhaled NO may exhibit promising antibacterial activity against MDR bacteria, clinical evidence regarding its use in critically ill patients with MDR pneumonia remains lacking.

Patel et al. [14] and Manda-Handzlik et al. [15] reported that NO promotes the generation of reactive species and stimulates the release of neutrophil extracellular traps (NETs), while peroxynitrite may facilitate NET formation. Experimental studies have further suggested that high-dose inhaled NO may enhance neutrophil chemotaxis and activation, neutrophil extracellular trap release, and bacterial killing [14–16]. However, these effects have not yet been demonstrated in humans. Because MDR severe pneumonia has high mortality and lacks effective adjunctive treatments, high-dose inhaled NO is a plausible therapeutic strategy. However, clinical data in patients with severe pneumonia associated with MDR bacteria remains insufficient.

This prospective randomized controlled trial will evaluate adjunctive high-dose inhaled NO therapy in mechanically ventilated patients with severe pneumonia caused by MDR bacteria. The trial will evaluate the efficacy and safety of high-dose inhaled NO therapy by assessing the Clinical Pulmonary Infection Score (CPIS), mortality, bacterial eradication rates, methemoglobin (MetHb) levels, and markers of kidney injury.

## Patients and methods

### Study design

This prospective, single-center, double-blind, randomized controlled trial will enroll consecutive eligible patients admitted to Jiangdu People’s Hospital Affiliated with Yangzhou University between January 2026 and June 2027 with suspected or confirmed severe pneumonia caused by MDR bacteria. The study flow is shown in Figure 1. The protocol follows the SPIRIT statement (Table 1; Table S1) [17].

**Figure 1. F0001:**
[figure not shown]
flow diagram of this trial. AST: Antimicrobial susceptibility testing; MDR: Multidrug-resistant; NO: Nitric oxide.

**Table 1. t0001:** Schedule of patient enrollment, study interventions, and outcome assessment according to SPIRIT statement.

			Study period									
	Enrollment		Post-randomization									
Timepoint	Admitted to the ICU	Suspected or confirmed MDR bacteria	Day1	Day2	Day3	Day4	Day5	Day6	Day7	ICU discharge	Hospital discharge	Day28
**Enrollment**												
Eligibility screen	X											
Inclusion criteria	X											
Written informed consent		X										
Exclusion criteria		X										
Baseline data		X										
Randomization		X										
**Study interventions**												
High-dose Nitric Oxide Inhalation		X	X	X	X	X	X	X	X			X
Control		X	X	X	X	X	X	X	X			
**Assessment**												
Change in CPIS			X		X				X			
ICU mortality rate										X		
Hospital mortality											X	
28-Day mortality rate												X
Ventilator-free days at day 28												X
Antibiotic-free days at day 28												X
SOFA score			X		X				X			
Citrullinated histone H3			X						X			
Cell-free DNA			X						X			
PaO_2_/FiO_2_			X	X	X	X	X	X	X			
Creatinine			X	X	X	X	X	X	X			
Methemoglobin			X	X	X	X	X	X	X			
NO₂			X	X	X	X	X	X	X			
AHR events			X	X	X	X	X	X	X			
AKI stages			X	X	X	X	X	X	X	X	X	

AHR events: airway hyperresponsiveness events; AKI: acute kidney injury; ICU: intensive care unit; MDR: multidrug-resistant; NO_2_: nitrogen dioxide; DNA: deoxyribonucleic acid; PaO_2_/FiO_2_: ratio of arterial oxygen partial pressure to fractional inspired oxygen; SOFA: Sequential Organ Failure Assessment.

### Ethics and registration

The study protocol was approved by the Ethics Committee of Jiangdu People’s Hospital Affiliated to Yangzhou University on 15 August 2025 (approval number: YJRY-2025-K-022). The trial was registered with the Chinese Clinical Trial Registry on 11 November 2025 (registration number: ChiCTR2500112185). All procedures will be conducted in accordance with the Declaration of Helsinki. Written informed consent will be obtained from each participant or legally authorized representative before enrollment.

### Participants

Eligible patients must meet all the following criteria:Age 18 years or older.Diagnosis of severe pneumonia within 24 h before enrolment.Requirement for invasive mechanical ventilation.Suspected or confirmed infection caused by multidrug-resistant (MDR) bacteria; confirmation may be based on sputum or bronchoalveolar lavage fluid (BALF) culture.Written informed consent provided by the patient or a legally authorized representative.

Informed by previous studies by Di Fenza et al. [18] and Kalashnikova et al. [8], patients will be excluded if they meet any of the following criteria:Current participation in another clinical trial;Active pulmonary malignancy or a history of lung transplantation or pulmonary resection;Severe burns involving >40% of the total body surface area;Severe hepatic or renal dysfunction, defined as Child–Pugh class C hepatic impairment or an estimated glomerular filtration rate <30 mL/min;Current receipt of renal replacement therapy;Previous inhaled NO therapy before enrolment;Patients with methemoglobinemia;Major bleeding at screening.

#### Definition of pneumonia

Pneumonia is defined as the presence of a new or progressive pulmonary infiltrate on chest imaging, together with at least one of the following clinical features of infection: (1) new-onset cough or sputum production, or worsening of pre-existing respiratory symptoms, with or without purulent sputum, pleuritic chest pain, dyspnea, or hemoptysis; (2) fever; or (3) a peripheral white blood cell count >10 × 10^9^/L or <4 × 10^9^/L, with or without a left shift.

#### Definition of severe pneumonia

Severe pneumonia is defined according to the ATS/IDSA criteria. Major criteria are respiratory failure requiring invasive mechanical ventilation and septic shock requiring vasopressor support. Minor criteria are a respiratory rate ≥30 breaths/min, a PaO_2_/FiO_2_ ratio ≤250 mmHg, multilobar infiltrates, confusion or disorientation, blood urea nitrogen ≥20 mg/dL, leukopenia (white blood cell count <4,000 cells/μL), thrombocytopenia (platelet count <100,000/μL), hypothermia (core body temperature <36 °C), and hypotension requiring aggressive fluid resuscitation. Severe pneumonia is diagnosed in the presence of at least one major criterion or at least three minor criteria [19].

#### Definition of MDR bacteria

MDR bacteria are defined as bacteria resistant to three or more commonly used classes of antimicrobial agents [20]. Common clinically important MDR pathogens include carbapenem-resistant *Acinetobacter baumannii* (CRAB), carbapenem-resistant *Pseudomonas aeruginosa* (CRPA), difficult-to-treat-resistant *P. aeruginosa* (DTR-PA), carbapenem-resistant Enterobacterales (CRE), *Stenotrophomonas maltophilia*, and methicillin-resistant *Staphylococcus aureus* (MRSA), and other MDR pathogens.

**Suspected MDR infection** is defined as the presence of at least one of the following: (1) previous respiratory isolation of methicillin-resistant *Staphylococcus aureus* (MRSA) or *Pseudomonas aeruginosa*; (2) hospitalization and exposure to intravenous antibiotics within the preceding 90 days; or (3) rapid microbiological testing suggestive of MDR pathogens [19,21,22].

#### Definition of major bleeding

1. Fatal bleeding, 2. Symptomatic bleeding in a critical area or organ, such as intracranial, intraspinal, intraocular, retroperitoneal, intra-articular or pericardial, or intramuscular with compart-ment syndrome,3. Bleeding causing a fall in hemoglobin level of 20 g/L) or more, or leading to transfusion of two or more units of whole blood or red cells [23].

#### Randomization and blinding

Participants will be randomly assigned in a 1:1 ratio to the high-dose inhaled NO group or the control group using a computer-generated simple randomization sequence. Allocation concealment will be maintained by an independent unblinded research staff member who is not involved in participant screening, clinical care, outcome assessment, data collection, or statistical analysis and who will retain the randomization codes.

Both groups will use identical NO delivery devices, respiratory circuit connections, treatment frequencies, and treatment durations. In the high-dose inhaled NO group, the device will operate in its standard mode to deliver the protocol-specified NO concentration. In the control group, the device will operate in a sham NO research mode. This mode will maintain the same user interface, operating procedures, and display of study-related parameters as in the intervention group, but will deliver gas containing no NO (NO concentration, 0 ppm).

For each treatment session, the independent unblinded research staff member will perform device connection, mode selection, parameter setting, and operational verification. This staff member will not participate in clinical care, outcome assessment, data collection, or statistical analysis and will not disclose device mode or treatment allocation to other study personnel or the clinical team. Participants, treating physicians, bedside clinical staff, outcome assessors, data collectors, and statisticians will remain blinded to treatment allocation.

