#### Sample size

As no previous studies have reported the effect of high-dose inhaled NO on CPIS outcomes in patients with severe pneumonia caused by MDR bacteria, the sample size was estimated using preliminary retrospective data from our center. These data included four patients who received high-dose inhaled NO and 11 patients who received standard treatment. The between-group difference in CPIS was 3 points, with a standard deviation of 4 points. Assuming a two-sided α of 0.05 and a β of 0.20 (80% power), at least 28 participants per group are required, for a total of 56 participants. Allowing a 10% dropout rate, the target sample size is 64 participants with confirmed MDR bacterial infection (32 per group). Assuming that 65% of patients with suspected MDR infection will have confirmed MDR bacterial infection, approximately 98 patients with suspected MDR infection will need to be enrolled.

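### Simple randomization and an unadjusted primary test leave chance imbalance in septic shock neither limited by design nor handled in the analysis

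*Protocol article*

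**What the plan says.** Under Randomization and blinding the article states: "Participants will be randomly assigned in a 1:1 ratio to the high-dose inhaled NO group or the control group", "using a computer-generated simple randomization sequence". It mentions no blocks, strata or minimization, and the word simple makes this a stated choice.

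Under Sample size the requirement is given per arm: "at least 28 participants per group are required, for a total of 56 participants". After a 10% dropout allowance this becomes 64 patients with confirmed MDR infection, 32 per group, drawn from about 98 enrolled on a 65% confirmation rate. The planning values are stated as "The between-group difference in CPIS was 3 points, with a standard deviation of 4 points".

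Under Analysis of populations the primary and secondary outcomes are analysed in the confirmed-MDR subset of those randomized. For patients enrolled on suspicion, confirmation can come after allocation. Under Statistical analysis the change in CPIS is compared by an independent-samples t test, or by a Wilcoxon rank-sum test if the data are not normal; no covariates are named. Under Subgroup and sensitivity analyses the primary outcome is examined by septic shock, by community- versus hospital-acquired pneumonia, and by use of inhaled antibiotics.

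**The concern.** By listing septic shock as a subgroup factor for the primary outcome, the authors show that they consider it relevant to CPIS. With about 64 analysed patients, unrestricted allocation can leave the arms visibly different in the share with shock. Two tools limit the consequence: stratifying the allocation, or adjusting the analysis. The article uses neither.

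At stake are the precision and credibility of a small single-centre trial. If the arms turn out to differ markedly in shock, part of the observed CPIS difference may be prognostic. The primary test described would not separate that part from the treatment effect, and an adjustment chosen after seeing the imbalance would carry little weight. The mortality comparisons are exposed in the same way.

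**Working it through.** **1. Reproducing the plan's sample size.** Inputs from the Sample size section: difference 3, SD 4, two-sided α 0.05, power 80%.

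- n per arm = 2 × [4 × (1.960 + 0.842) / 3]² = 27.9, rounded up to 28. This agrees with the article.
- 28 / 0.90 = 31.1, rounded up to 32 per arm, 64 in total. This agrees.
- 64 / 0.65 = 98.5, against about 98 stated. This agrees.
- By the noncentral t distribution, 28 per arm gives 78.7% power and 29 per arm gives 80.1%. The gap from 80% is trivial.

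**2. Arm sizes under simple randomization, 64 analysed.** The size of one arm is Binomial(64, 0.5), with mean 32 and SD √64 / 2 = 4.0.

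- P(exactly 32/32) = 9.9%.
- P(smaller arm 27 or fewer, before dropout) = 26.0%.
- 95% range: 24/40 to 40/24.

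**3. What unequal arms cost.** The equivalent size per arm is 2·n₁·n₂ / (n₁ + n₂). Power is by noncentral t with difference 3 and SD 4.

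| Split | Equivalent per arm | Power |
|---|---|---|
| 32/32 | 32.0 | 84.0% |
| 27/37 | 31.2 | 83.1% |
| 24/40 | 30.0 | 81.6% |
| 21/43 | 28.2 | 79.2% |
| 28/28 (stated requirement) | 28.0 | 78.7% |

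Precision falls below that of 28/28 only when the smaller arm has 20 or fewer of the 64, which has probability 0.4%. Averaged over the allocation distribution, power is 83.4% against 84.0% at 64 analysed, 79.4% against 80.1% at 58, and 78.0% against 78.7% at 56. The average loss is about 0.6 to 0.7 points.

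**4. Imbalance in septic shock.** The prevalence p is assumed to be 30% to 50%. With about 32 per arm, the SD of the difference in proportions is √[p(1 − p) × 2/32]: 0.115 at p = 0.3 and 0.125 at p = 0.5. A difference of 0.20 is then about 1.7 or 1.6 SDs. Simulation of simple randomization with 64 analysed gives:

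| Assumed prevalence | Differ by ≥15 points | Differ by ≥20 points |
|---|---|---|
| 30% | 19% | 8% |
| 40% | 23% | 11% |
| 50% | 25% | 11% |

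**5. What each remedy does.** Forcing 32/32 without stratifying leaves P(≥20 points) at 8% to 10%, so blocking alone barely helps. With 98 enrolled in blocks of 4 stratified by shock and a random 64 confirmed, P(≥20 points) falls to about 0.5% to 0.7% and P(≥15 points) to about 3% to 6%.

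**6. What a realised imbalance could do (illustration).** Suppose shock shifts the CPIS change by 3 points, an assumed figure, and the arms differ by 20 points. The unadjusted estimate moves by 3 × 0.20 = 0.6. The standard error at 32/32 is 4 × √(2/32) = 1.0. Given that imbalance, the false-positive rate is about 9% instead of 5%. With a 2-point shift (0.4) it is about 7%.

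**The case against.** The strongest reply is that simple randomization is valid. Over all possible allocations the nominal α already covers chance imbalance in every covariate, and the estimate is unbiased. That stands. The raised rates in step 6 are conditional on an unlucky allocation; they do not mean that the trial's overall type I error is inflated.

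A reader might also infer that the plan will miss its own requirement, since one arm has fewer than 28 patients in 26% of allocations. The document does not support that reading. Under 1:1 allocation 32 per group is an expected size, and the requirement of 28 per group assumes equal arms. A 27/37 split has more power than 28/28. Nor would blocking secure 32 per group, because confirmation can follow allocation: even with 98 enrolled split exactly 49/49, an exact 32/32 among 64 confirmed has probability only 16.8%.

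Three further replies carry less weight.

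- Change from baseline absorbs some of the difference in starting CPIS, but it does not deal with shock as a separate predictor of the course to day 7.
- The septic shock subgroup analysis describes effects within subgroups; it does not adjust the overall comparison.
- Covariate adjustment is often left to an analysis plan, which is not shown here. The article, however, states the test for CPIS change, and that test is unadjusted.

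Predictability is a fair cost to raise. Simple randomization is the hardest scheme to guess, and the Discussion says that the trial is single-blind with medical staff unblinded, whereas Randomization and blinding says that treating physicians and bedside staff are blinded. If staff do know the allocations, blocks become easier to guess. This weighs on the blocking part of the remedy and leaves the adjusted model untouched.

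**Conclusion.** The point holds as an improvement in balance, precision and credibility, not as an error. Septic shock, which the article itself treats as relevant to the primary outcome, is neither balanced by the allocation nor included in the stated test. At an assumed prevalence of 30% to 50%, a difference of 20 points or more between arms has probability 8% to 11%, and stratification would bring this to about 0.5% to 0.7%.

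The sample size reproduces, inference is valid, and the average power cost of unequal arms is about 0.6 to 0.7 points. The article gives neither a prevalence of shock nor the strength of its association with CPIS change, so the resulting shift in the estimate or loss of precision can only be illustrated.

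**What to change.** - **Allocation.** Replace the simple sequence with permuted blocks of randomly varying, concealed size, stratified by septic shock at enrolment and optionally by confirmed versus suspected MDR infection at enrolment. The independent staff member who already holds the codes can keep the list.
- **Analysis.** Replace the unadjusted primary test with a linear model for CPIS change containing treatment, septic shock and the other stratification factor if it is used, all prespecified.
- **If enrolment has begun.** Adopt at least the adjusted model, by dated amendment before unblinding. Changing the allocation scheme for the remaining patients is optional, and mixes two mechanisms in a small trial.
- **First.** Reconcile Randomization and blinding with the limitations paragraph of the Discussion on whether clinical staff are blinded, since this decides how much the predictability of blocks matters.
- **Wording.** Describe 32 per group as the expected size.

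The cost is a new list, a short amendment and slight predictability of blocks. The adjusted model has almost no downside.

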#### Emergency unblinding criteria

Emergency unblinding will be permitted only for a life-threatening medical event or an event that may result in irreversible harm, when the investigator determines that knowledge of the study gas received by the participant is necessary for immediate resuscitation or subsequent critical treatment decisions.

Individual emergency unblinding may be considered if any of the following occurs:Uncontrolled respiratory or hemodynamic deterioration, including persistent hypoxemia, urgent escalation of respiratory support, circulatory shock, severe arrhythmia, or cardiac arrest, when knowledge of whether the participant received inhaled NO would alter immediate clinical management.A suspected serious adverse reaction or serious unexpected medical event related to study gas, for which treatment allocation remains necessary to guide further management after discontinuation of the study gas and standard clinical treatment.Any other emergency that is life-threatening or may result in irreversible harm, when the investigator determines that failure to unblind would compromise participant safety.

#### Interventions

Participants in the intervention group will receive iNO at 200 ppm two times daily, with each session lasting 30 min, for 5 days, beginning within 24 h of enrollment [8]. Both the intervention and control groups will receive standard treatment according to relevant guidelines for severe pneumonia. Standard treatment may include empirical and targeted anti-infective therapy, fluid resuscitation, vasoactive drugs, lung-protective ventilation, organ support, nutritional support, and immunomodulatory therapy as clinically indicated. Once antimicrobial susceptibility results are available, participants in both groups with confirmed MDR bacterial infection will continue the protocol-directed study intervention. For participants in whom MDR bacterial infection is not confirmed, the study intervention administered solely for research purposes will be discontinued in both groups.

Inhaled NO will be administered using the NOwill N300 Nitric Oxide Generation and Delivery System (Noling Biotechnology Co., Ltd., Nanjing, China). All device installation, mode selection, circuit connection, pre-treatment safety checks, and monitoring during treatment will be performed exclusively by designated independent research personnel who have completed manufacturer training and are qualified to operate the system. These personnel will not participate in participant screening, routine clinical care, outcome assessment, data collection, or statistical analysis.

At enrolment, inhaled NO will be delivered through the mechanical ventilator circuit. If a participant is extubated during the treatment period, inhaled NO will be administered through an interface compatible with the selected sequential oxygen therapy modality.

The NOwill N300 system may be connected to invasive ventilators, noninvasive ventilators, high-flow oxygen therapy systems, nasal cannulae, or face masks. For participants receiving invasive mechanical ventilation, the NO delivery device will be integrated into the ventilator circuit at the gas outlet, with a flow sensor and NO injection port installed. The NO injection port will be positioned upstream of the humidification chamber to enable NO delivery during the inspiratory phase.

The NO sampling port will be placed on the inspiratory limb close to the patient and at least 15 cm from the Y-piece. Connections to noninvasive ventilation and high-flow oxygen therapy systems will follow the same principles. During noninvasive ventilation, the NO sampling port will be positioned at least 15 cm from the exhalation valve.

Before and throughout each treatment session, dedicated study personnel will continuously monitor inspired NO concentration, NO_2_ concentration, oxygen concentration, device operating status, and alarm notifications.

